# Robotic-arm assisted medial unicondylar knee arthroplasty versus jig-based unicompartmental knee arthroplasty with navigation control: study protocol for a prospective randomised controlled trial

**DOI:** 10.1186/s13063-020-04631-5

**Published:** 2020-08-17

## Abstract

**Background:**

There remains a paucity of clinical studies assessing how any differences in accuracy of implant positioning between robotic-arm assisted unicompartmental knee arthroplasty (RO UKA) and conventional jig-based unicompartmental knee arthroplasty (CO UKA) translate to patient satisfaction, functional outcomes, and implant survivorship. The objectives of this study are to compare accuracy of implant positioning, limb alignment, patient satisfaction, functional outcomes, implant survivorship, cost-effectiveness, and complications in CO UKA versus RO UKA. Computer navigation will be used to assess intraoperative knee kinematics in all patients undergoing CO UKA.

**Methods and analysis:**

This prospective randomised controlled trial will include 140 patients with symptomatic medial compartment knee arthritis undergoing primary UKA. Following informed consent, patients will be randomised to CO UKA (control group) or RO UKA (investigation group) at a ratio of 1:1 using an online random number generator. The primary objective of this study is to compare accuracy of implant positioning in CO UKA versus RO UKA. The secondary objectives are to compare the following outcomes between the two treatment groups: limb alignment, surgical efficiency, postoperative functional rehabilitation, functional outcomes, quality of life, range of motion, resource use, cost effectivness, and complications. Observers will review patients at regular intervals for 2 years after surgery to record predefined study outcomes pertaining to these objectives. Ethical approval was obtained from the London-Bloomsbury Research Ethics Committee, UK. The study is sponsored by University College London, UK.

**Discussion:**

This study compares a comprehensive and robust range of clinical, functional, and radiological outcomes in CO UKA versus RO UKA. The findings of this study will provide an improved understanding of the differences in CO UKA versus RO UKA with respect to accuracy of implant positioning, patient satisfaction, functional outcomes, implant survivorship, cost-effectiveness, and complications.

**Trial registration:**

ClinicalTrials.gov NCT04095637. Registered on 19 September 2019.

## Background

Unicompartmental knee arthroplasty (UKA) is an established and highly effective treatment for patients with end-stage arthritis affecting a single compartment of the knee joint [2]. The procedure accounts for between 8 and 10% of all knee arthroplasty procedures performed in the UK [1, 15]. There are several advantages of performing UKA over total knee arthroplasty (TKA), including reduced operating time, decreased intraoperative blood loss, reduced periarticular soft tissue trauma, improved preservation of bone stock, better restoration of native kinematics, increased patient satisfaction, and improved functional outcomes [7, 16, 20, 21, 34, 35]. However, UKA is associated with decreased implant survivorship and increased revision rates compared with TKA [9, 28]. Accuracy of component positioning and limb alignment are important prognostic variables that affect implant survival and time to revision surgery following UKA [5, 9, 38]. Consequently, techniques that improve the accuracy of implant positioning and limb alignment in UKA may help to improve long-term survivorship and reduce the burden of revision disease. Conventional jig-based UKA (CO UKA) is performed using manually positioned alignment guides and cutting blocks, limited intraoperative data on knee kinematics, and handheld milling devices or sawblades for bone resection. These techniques are highly dependent on the skill and expertise of the operating surgeons [32, 34]. Studies using data from three separate national joint registries have demonstrated a relationship between the surgical (or unit) case-load and revision rate following UKA [29–32]. Surgeon-controlled errors in implant positioning are the most common reason for implant failure, and low case-volume has been identified as a risk factor for early revision surgery following UKA [30, 32].

Evolution in surgical technology has led to the development of robotic-arm assisted UKA (RO UKA). This uses a preoperative computerised tomography (CT) scan to create a patient-specific virtual three-dimensional reconstruction of the knee joint. The surgeon uses this virtual model to plan optimal bone coverage, implant positioning, and limb alignment for each patient’s unique knee anatomy. An intraoperative robotic arm then helps to execute this plan with a high-level of accuracy, and stereotactic boundaries limit bone resection to the predefined femoral and tibial haptic windows [4, 26, 37]. Intraoperative optical motion capture technology provides real-time medial and lateral gap measurements whilst applying valgus/varus strains to appropriately tension the ligaments through the arc of flexion [10, 24, 26]. Intraoperative data on the ‘tightness’ and ‘looseness’ of the knee joint through the arc of flexion may be used to further adjust bone resection, implant sizes, and implant positions to achieve the desired knee kinematics. Aseptic loosening and progression of osteoarthritis in the remaining native knee compartments are common reasons for failure in UKA [8, 15, 16]. RO UKA enables accurate intraoperative assessment of limb alignment to avoid overcorrection, which may reduce disease progression in the remaining native compartments and help to improve overall implant survivorship. Improved accuracy of bone resection within the confines of the predefined stereotactic boundaries may also reduce periarticular soft tissue injury and enhance postoperative rehabilitation compared to CO UKA [25, 37]. Initial studies have shown that RO UKA is associated with improved accuracy of implant positioning, reduced outliers in limb alignment, faster postoperative rehabilitation, earlier time to hospital discharge, and improved implant survivorship compared to CO UKA [4, 6, 10, 26, 27, 36].

Despite these promising preliminary results with RO UKA, there remains a paucity of high-quality studies comparing a comprehensive and robust range of clinical, functional, and radiological outcomes to CO UKA. Cobb et al. conducted a prospective randomised study on 27 patients with medial compartment knee osteoarthritis undergoing CO UKA versus RO UKA [10]. The authors reported that all patients undergoing RO UKA had tibiofemoral alignment in the coronal plane within 2° of the planned position compared with only 40% in those undergoing CO UKA. Bell et al. performed a prospective randomised controlled study assessing accuracy of implant positioning using postoperative CT scans in 62 RO UKAs versus 58 CO UKAs and found that RO UKA reduced root mean square errors in achieving planned femoral and tibial implant positioning [4]. Blyth et al. followed these patients and found RO UKA was associated with reduced median pain scores by 55.4% compared with CO UKA from postoperative day 1 to week 8 after surgery [6]. RO UKA was associated with improved American Knee Society Score for 3 months following surgery, but there was no difference in functional outcomes observed between CO UKA and RO UKA at 1 year after surgery. Subgroup analysis of the 35 most active patients revealed robotic UKA improved Knee Society Scores, Oxford Knee Scores, and Forgotten Joint Scores compared with CO UKA at 2 years’ follow-up. Herry et al. reviewed plain radiographs in 40 CO UKAs versus 40 RO UKAs and found improved restitution of the native joint line with robotic-guided surgery [18]. Kayani et al. conducted a prospective cohort study on 146 patients showing RO UKA was associated with reduced postoperative pain, decreased opiate analgesia consumption, reduced need for inpatient physiotherapy sessions, and decreased mean time to hospital discharge compared with CO UKA [27]. The main limitations of the aforementioned studies were that outcomes were recorded by non-blinded observers, surgery was undertaken by multiple surgeons with varying experience in UKA, and only limited clinical or functional outcomes were presented at short-term follow-up.

The delayed uptake of RO UKA has been attributed to the substantive installation and maintenance costs of this technology and limited data showing any clinical or functional benefit to an already well-established and successful CO UKA [4, 6, 8, 15, 26, 34, 35]. Pearle et al. conducted a prospective, multicentre review of 1135 RO UKAs and found implant survivorship was 98.8% at a minimum of 22 months’ follow-up, which is superior to the survival rates of CO UKA reported in the national joint registries of the UK (95.6%), Sweden (95.3%), Australia (95.1%), and New Zealand (96.1%) [36]. Batailler et al. compared outcomes in 80 CO UKAs versus 80 RO UKAs and found revision rates in RO UKA were 5% compared with 9% in CO UKA, although this difference was not statistically significant [3]. Moschetti et al. used a Markov decision analysis tool to compare cost-effectiveness of CO UKA versus RO UKA [33]. Using a 2-year failure rate of 1.2% for RO UKA and 3.1% for CO UKA, the authors reported that RO UKA was a cost-effective procedure only if RO UKA case-volume exceeded 94 cases per year. The main limitations of this study were that it did not include the additional costs associated with purchasing the robotic device, buying new implants compatible with the robotic computer software, additional training for the surgical team, increased operative times during the learning phase, and patient resource use. There remains a paucity of data on how RO UKA impacts functional outcomes, quality-adjusted-life years (QALYs), implant survivorship, and cumulative revision rates compared to CO UKA.

In the proposed study, we aim to improve on existing trials by assessing a more comprehensive and robust range of functional and radiological outcomes, prospectively randomising patients to their treatment groups, using standardised surgical techniques in each treatment group, and collecting data at regular follow-up intervals after surgery. This study aims to build on the previous trials by Bell et al. and Blyth et al. by using three-dimensional preoperative templating in both treatment groups, inserting navigation pins to assess knee kinematics and limb alignment in CO UKA, assessing a more comprehensive range of functional outcome scores, blinding patients and observers recording clinical outcomes, and recording study outcomes for a robust analysis of cost-effectiveness and resource use between the two treatment groups [4, 6, 14]. The findings of this study will enable an improved understanding of differences in CO UKA versus RO UKA with respect to patient satisfaction, functional outcomes, implant survivorship, cost-effectiveness, and complications.

## Methods/design

### Objectives

The primary objective of this study is to compare accuracy of implant positioning in CO UKA versus RO UKA. Accuracy of implant positioning will be assessed by measuring differences in the planned implant position on preoperative CT scan versus the achieved implant position on postoperative CT scan. The null hypothesis is that there is no difference in accuracy of implant positioning between CO UKA versus RO UKA.

The secondary objectives are to compare the following outcomes between the two treatment groups:
Limb alignmentSurgical efficiencyPostoperative functional rehabilitationFunctional outcomesQuality of lifeRange of motionMobilisation distanceResource use and cost effectivenessComplications

### Trial design

This study is a prospective, single-centre, randomised controlled trial. The study will be undertaken in the Department of Trauma and Orthopaedics, University College Hospital, [name], UK. The study will include 140 patients randomly allocated to either CO UKA (control group) or RO UKA (investigation group). The Oxford UKA was selected as the comparator as this was the most commonly used implant for UKA by all three operating surgeons at the study hospital and the most commonly used implant for UKA within the UK [1]. The study commenced patient recruitment in November 2017 and is expected to complete patient recruitment in April 2021. All patients will be followed up for 2 years after surgery, and therefore, the anticipated completion date for the study is April 2023. The study is sponsored by University College London, UK. The patient enrolment flowchart is presented in Fig. 1. The schedule of enrolment, interventions, and assessments for all study patients is shown in Fig. 2.

**Fig. 1 Fig1:**
[figure not shown]
Patient enrolment flow chart

**Fig. 2 Fig2:**
[figure not shown]
Schedule of enrolment, interventions, and assessments for all study patients. CO UKA, conventional jig-based unicompartmental knee arthroplasty; RO UKA, robotic-arm-assisted unicompartmental knee arthroplasty; CT, computerised tomography

### Eligibility criteria

The inclusion criteria for this study are as follows: patient has symptomatic medial knee compartment arthritis requiring primary medial UKA, patient fit for surgical intervention following review by surgeon and anaesthetist, patient aged between 18 and 80 years at time of surgery, patient able to give informed consent and agrees to comply with the postoperative review programme, and patient has sufficient mobility to attend follow-up clinics. The exclusion criteria for this study are as follows: patient undergoing revision surgery following previously failed correctional osteotomy or ipsilateral UKA; patient not suitable for UKA (e.g. multi-compartment knee disease or ruptured anterior cruciate ligament); patient is immobile or has another neurological condition affecting musculoskeletal function; patient already enrolled on another concurrent clinical trial; patient unable or unwilling to sign the informed consent form specific to this study; and patient unable to attend the study follow-up programme.

### Recruitment

Patients will be recruited from the orthopaedic outpatient clinic at University College Hospital, London, UK. All patients will be screened by the clinical team (orthopaedic consultant surgeon, clinical research fellow, and orthopaedic registrar) for study participation based on the predefined inclusion and exclusion criteria listed above. Patients that fulfil the eligibility criteria and express an interest to participate in the study will be provided with an ethics committee-approved patient information sheet. This provides details about the study treatment, follow-up and contact details for further information. All members of the clinical team are familiar with the study and will address any preliminary questions about the study. Details of those patients expressing an interest to participate in the study will be recorded in the patient contact form and forwarded to the research physiotherapist. The research physiotherapist will phone the patient 4 weeks after this consultation to discuss any further questions and confirm if the patient would like to participate in the study.

### Consent

Informed consent will be obtained by the chief investigator or principal investigator when the patient attends for the preoperative planning CT scan. This is 6 weeks after the outpatient consultation for agreement to UKA and 2 weeks before surgery. It is important to the data collection scheme that patients are able to follow commands and read and interpret questions via questionnaires. For those who cannot hear, read, or understand English, an interpreter will be provided. Identical preoperative imaging modalities for surgical planning will be used in both treatment groups.

### Allocation

After informed consent has been obtained, the research physiotherapist will randomise the patient into one of the two treatment groups using an online random number generator (www.random.org). A number from 1 to 140 can be randomly generated and will allocate each patient to one of the two arms of the study: 1–70 inclusive for the control group, 71–140 inclusive for the investigation group. The research physiotherapist will perform the randomisation procedure and store the designated treatment group for each patient on a password-encrypted file on the hospital computer. The operating surgeon will have this information communicated to him on the morning of surgery.

### Preoperative imaging

All study patients will undergo preoperative long-leg alignment radiographs, anteroposterior and lateral knee radiographs, and CT scans of the knee joint. In both treatment groups, plain radiographs will be exported onto Traumacad software (Traumacad, Petach-Tikva, Israel) to template implant positioning and sizes for achieving the planned bone coverage, component position, and limb alignment. In CO UKA, fixed target values for component implantation will be obtained from the manufacturer’s manual, and the preoperative CT scans will be used to fine-tune bone resection and implant positioning. In RO UKA, preoperative CT scans will be exported onto a computer software programme (Mako system software, Stryker Limited, Kalamazoo, MI) to create a patient-specific, three-dimensional, computer-aided design model of the patient’s knee anatomy. This will be used to create a preoperative surgical plan for implant positioning. Intraoperative assessments of soft tissue tension, gap measurements, and limb alignment will be used to fine-tune bone resection and guide definitive component implantation. All preoperative templating will be undertaken by the senior supervising surgeon 2 weeks before surgery. Preoperative CT scans are not routinely used for preoperative surgical planning in CO UKA. However, both treatment groups in this study will have preoperative CT scans for three-dimensional surgical planning. This will help to limit any confounding effects from differences in preoperative planning techniques between the two treatment groups impacting the study outcomes.

RO UKA will be undertaken using extra-incisional bicortical femoral and tibial registration pins with fixed infra-red arrays mounted onto these to enable intraoperative optical motion capture technology to assess knee kinematics and alignment. Bone registration will be performed by mapping radiological landmarks displayed on the computer screen to register and verify osseous anatomy and bone geometry. Joint balancing will be used to capture femoral and tibial poses with corrective valgus and varus forces to assess knee kinematics through the arc of motion, and fine-tune implant positioning based on laxity of the soft tissue envelope. Bone resection will be performed within the stereotactic boundaries of the haptic bone windows using a high-speed, water-cooled burr with tactile, visual, and audio feedback. Optical motion capture technology will be used to assess limb alignment, flexion-extension gaps, mediolateral laxity, and range of motion with trial implants prior to definitive selection and cement implantation of final components. The RESTORIS MCK (Mako Surgical Corporation, Kalamazoo, Michigan) fixed-bearing UKA system will be implanted using the RIO robotic interactive arm orthopaedic system (Mako Surgical Corporation, Stryker, Kalmazoo, USA) in all patients undergoing RO UKA.

### Outcomes

All study patients will undergo review by two blinded observers (one orthopaedic registrar and one clinical research fellow) at 6 weeks, 6 months, 1 year, and 2 years following surgery. During these follow-up times, predefined clinical outcomes will be recorded by these observers using case report forms (CRFs). In addition, three independent observers (clinical research fellows) will collect radiological outcomes. It is not possible to blind observers recording radiological outcomes as different implant designs will be used within each treatment group. However, the three observers will independently calculate the accuracy of femoral and tibial implant positioning in each patient, and interobserver agreement for all radiological outcomes will be investigated using interclass correlation coefficients.

The following outcomes will be recorded in all study patients:
Accuracy of achieving the planned implant positioning as assessed using CT scans performed postoperatively at 6 weeks.Operating time (minutes)Time to hospital discharge (hours)Analgesia requirements during inpatient admission and postoperatively at 6 weeks, 6 months, 1 year, and 2 yearsPatient-reported outcome measures including Oxford knee score (OKS) and short form (SF-12), Western Ontario and McMaster Universities Arthritis Index (WOMAC), Knee injury and Osteoarthritis Outcome Score (KOOS), and University College Hospital (UCH) functional score during inpatient admission and postoperatively at 6 weeks, 6 months, 1 year, and 2 years.Health-related quality of life as measured using European Quality of Life questionnaire with 5 dimensions for adults (EQ-5D) preoperatively and postoperatively at 6 weeks, 6 months, 1 year, and 2 yearsMobilisation distance (metres) and use of mobility aids during inpatient admission and postoperatively at 6 weeks, 6 months, 1 year, and 2 yearsRange of movement (degrees) in the knee joint during inpatient admission and postoperatively at 6 weeks, 6 months, 1 year, and 2 yearsResource use and cost-effectiveness including comparisons between the two treatment groups relating to: Operating time, theatre efficiency, equipment and sterilisation costs, analgesia requirements, inpatient rehabilitation, time to discharge, outpatient follow-up, additional imaging costs, and need for further surgery.Complications

All patients will undergo preoperative and postoperative CT scans of the knee joint using a standardised protocol within a dedicated research scanner in the study hospital. The CT scans will be uploaded in DICOM (Digital Imaging and Communication in Medicine) format and then loaded onto Mimics software (Materialise) to calculate the accuracy of implant positioning. Accuracy of implant positioning will be assessed by comparing differences in the target values in the preoperative plan to the achieved values in the postoperative scan. These outcomes will be used to calculate root mean square errors values for accuracy of femoral and tibial component positioning within the coronal, sagittal, and axial planes as described by Bell et al. [4]. The posterior condylar offset ratio (PCOR) and posterior tibial slope will be assessed using the methods described by Gaudiani et al. and Johal et al. respectively [13, 23].

The WOMAC, OKS, SF-12, EQ-5D, and KOOS are validated tools for the clinical assessment of patients after knee arthroplasty [11, 12, 17, 22, 39]. In addition, the observers will calculate the UCH knee score to assess overall, pain, function, and mobility [19]. This will help to overcome any potential ceiling effect with the OKS and WOMAC and facilitate further subgroup analysis in patients with high functional demands [19]. Each of these clinician- and patient-reported scores will be collected preoperatively at the time of consenting to the study and also postoperatively at 6 weeks, 6 months, 1 year, and 2 years after surgery.

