### Sample size

Using the study by Bell et al. assessing differences in accuracy of component positioning between conventional and robotic UKA, the mean difference in femoral sagittal component positioning was set at 2° and standard deviation assumed at 4° [4]. Using a two-tailed, two-sample *t* test with a power of 80% (1–β), significance level of 5%, and an effect size of 0.5, this study required 128 patients to detect this minimum difference between the two treatment groups. To account for 10% attrition in the sample size during follow-up, the sample size was set at 140 patients.

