### Statistical analysis

The analysis of the per-protocol population will be considered the primary analysis. The differences between the CO UKA and RO UKA groups will be analysed by calculating the difference from baseline, per patient, and a two-sided confidence interval for the difference between the changes from baseline values will be calculated. This confidence interval will cover the true difference in the percentage change from baseline with a probability of 95%. The following statistical methods will be employed to analyse the data: descriptive statistics, independent *t* test, paired *t* test, analysis of variance, Fisher’s exact test, chi-square test, and graphical displays. Assumptions of normality will be tested with the D’Agostino test. Assumptions of homogeneity of variance will be tested with Levene’s test. If the distributional assumptions are (severely) violated, non-parametric techniques, such as Mann-Whitney’s test, will be employed. In the event that RO UKA is converted to CO UKA intraoperatively, analysis will be performed using the intention-to-treat population and the treatment actually received by the patients. Intraoperative conversion from RO UKA to CO UKA will be documented and presented and published as part of the study. The Bonferroni correction will be used to determine the level of significance due to multiple comparisons of secondary outcomes. Statistical significance is set at a *p* value < 0.05 for all analyses, and all statistical analysis will be performed using SPSS software version 26 (SPSS Inc., Chicago, IL, USA).

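### The general rule that sends severely non-normal data to rank tests makes no exception for costs, although cost-effectiveness depends on the difference in arithmetic mean cost

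*Protocol article*

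**What the plan says.** All references are to the protocol article.

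- **Objectives** lists resource use and cost effectiveness among the secondary objectives. **Background** names QALYs as an evidence gap and says the trial improves on earlier ones by "recording study outcomes for a robust analysis of cost-effectiveness and resource use between the two treatment groups".
- **Outcomes** describes resource use and cost-effectiveness as comparisons between the two groups on a list beginning "Operating time, theatre efficiency, equipment and sterilisation costs". The list goes on through analgesia, rehabilitation, discharge, follow-up and imaging to further surgery. It opens with the word *including*, and it names no total cost per patient. EQ-5D is a separate outcome, collected preoperatively and at 6 weeks, 6 months, 1 year and 2 years.
- **Statistical analysis** lists the methods: "descriptive statistics, independent *t* test, paired *t* test, analysis of variance, Fisher’s exact test, chi-square test, and graphical displays". It adds: "Assumptions of normality will be tested with the D’Agostino test". Then: "If the distributional assumptions are (severely) violated, non-parametric techniques, such as Mann-Whitney’s test, will be employed". Bonferroni applies to multiple comparisons of secondary outcomes, and the significance threshold is set for all analyses. No exception is made for costs. The one estimate it names is "a two-sided confidence interval for the difference between the changes from baseline values will be calculated".

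**The concern.** A cost comparison is useful to a payer only through the arithmetic mean, because mean cost times the number of patients is the budget. Further surgery is on the resource list. It affects few patients and is expensive, so it produces a long right tail. That tail is likely to make the normality check fail, and it also carries much of any difference in mean cost. A rank test largely discards the size of those few large values. The general rule would therefore set the mean comparison aside in just the situation where the tail matters.

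The named estimate does not fill the gap: a change from baseline has no meaning for costs, which have no baseline value. Bonferroni fits poorly too, since a cost-effectiveness result rests on joint estimates of cost and effect with their uncertainty, not on a series of significance tests.

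At stake is a secondary objective. The primary outcome is not affected.

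**Working it through.** **Arm size.** The Sample size section assumes a difference of 2° and an SD of 4°, so d = 2/4 = 0.5. A two-sided 5% t test with 80% power needs 63.77, rounded up to 64 per arm, or 128 in total, which matches the stated figure. It has no bearing on costs except to supply 64 per arm for the checks below. No figure for cost-effectiveness is stated, so there is none to reproduce.

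**Check 1: equal true means, different skewness.** Lognormal costs scaled to mean 1 in both arms, 5,000 simulated trials. The log-SDs are assumptions. With mean 1 the median is exp(−σ²/2): for σ = 0.5, exp(−0.125) = 0.88; for σ = 1.0, exp(−0.5) = 0.61. Equal means can therefore go with clearly different ranks.

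| log-SD, arm 1 / arm 2 | Mann-Whitney p < 0.05 | Welch t p < 0.05 |
|---|---|---|
| 0.5 / 0.5 | 4.5% | 4.8% |
| 0.5 / 1.0 | 73.4% | 7.6% |
| 0.3 / 0.8 | 68.9% | 6.4% |

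The D'Agostino test rejected normality in at least one arm in 99% or more of trials in every row. The rank test answers a different question from the mean comparison when skewness differs between arms, and does no harm here when it does not.

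**Check 2: a few expensive further operations.** Assumptions: index cost lognormal, mean 6,000 and SD 900; further surgery costs 12,000; RO UKA adds 200, 300 or 400 to the index cost. Background supplies two pairs of rates: revision 9% CO and 5% RO from a comparison of 80 against 80, and 2-year failure 3.1% CO and 1.2% RO from a decision model.

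True mean difference (RO minus CO) = added index cost − (CO rate − RO rate) × 12,000.

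| Added index cost | Rates 9% / 5% | Rates 3.1% / 1.2% |
|---|---|---|
| +200 | 200 − 480 = −280 | 200 − 228 = −28 |
| +300 | 300 − 480 = −180 | 300 − 228 = +72 |
| +400 | 400 − 480 = −80 | 400 − 228 = +172 |

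- With 9%/5%, D'Agostino rejects in about 100% of trials. Mann-Whitney is significant in about 10%, 21–23% and 41–42% for +200, +300 and +400, and 97–100% of those results show RO UKA as dearer although its true mean cost is lower. Welch's test is significant in 7%, 5% and 5%.
- With 3.1%/1.2%, D'Agostino rejects in 96–97%. At +200 Mann-Whitney is significant in 17%, 99% of those showing RO UKA as dearer, against a true difference of only −28. At +300 and +400 the rank test and the mean agree in sign.
- Bonferroni shrinks these rates. At an assumed threshold of 0.05/10 = 0.005, the +300 case with 9%/5% falls from 21% to 5%, and the +200 case from 10% to 2%.

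Failure of the normality check is common to every scenario tried. The reversal of sign is not.

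**The case against.** The strongest case against is that this is a condensed article and that silence is being read as a plan. Costing methods, QALY calculation and cost-effectiveness ratios are commonly left to a full protocol, analysis plan or health-economic plan, and none is shown. That stands: their absence is no finding.

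A reader might infer that the trial will produce no mean cost difference and no cost per QALY. The documents do not support this. No section says so; *including* leaves the list open; descriptive statistics are among the listed methods and could report mean costs; and EQ-5D at five times supplies what QALYs need.

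The rank-test rule is also softer than a mechanical switch. It applies when assumptions are severely violated, and Mann-Whitney is given only as an example. A significant D'Agostino test is not stated to be enough by itself. That this section governs the economic analysis is an inference, though a fair one, since its threshold covers all analyses.

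A reader might further infer that the rank test would point the opposite way from the true mean. That depends on invented costs and on the 9%/5% rates, which come from a comparison reported as not statistically significant and without a stated follow-up time. With the 2-year rates the reversal disappears in two of three scenarios and is trivial in the third. Check 2 also tests a total cost per patient, which the Outcomes list does not name. Compared item by item, further surgery would be a yes/no outcome for Fisher's or the chi-square test, and its cost would not enter a rank test at all.

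What survives is the stated rule itself: it covers secondary outcomes in general, exempts nothing, and does not suit costs.

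**Conclusion.** The point holds in a limited form. The Statistical analysis section fixes a general rule that, applied to costs, would probably replace the mean comparison with a rank test that does not estimate the quantity cost-effectiveness depends on. An economic plan that analysed mean costs would need an exception that this section does not give.

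The size cannot be fixed from the documents, because they hold no cost data. Under the assumptions of check 1, the rank test's rejection rate with equal mean costs ranges from about 5% (equal skewness) to 73% (unequal skewness). Under those of check 2, agreement in sign depends on the revision rates and index cost chosen, so the sign reversal is an illustration and not a prediction.

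The point concerns one secondary objective. It is worth correcting because the remedy is cheap and because choosing the cost analysis after seeing the 2-year data would be open to criticism.

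**What to change.** In the Statistical analysis section, exempt total cost per patient and QALYs from the normality switch and from Bonferroni, and state that:

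- total 2-year cost is computed for each patient and compared by the difference in arithmetic means;
- QALYs are the area under EQ-5D at the five collected times, with the difference in means adjusted for preoperative EQ-5D;
- both differences are reported with bootstrap intervals, resampling cost and QALYs together for each patient, and combined as incremental net benefit;
- item-by-item resource comparisons are descriptive.

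If a health-economic plan already does this, a sentence citing it, with the exemption, is enough.

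The cost is wording and a little analyst time. EQ-5D and the listed resource items are already collected. Intervals for mean cost may be wide, since the trial was sized for implant position; that is an honest statement of what it can say about cost. The change should be fixed before the 2-year data are analysed.
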